##### Breastfeeding Self-Efficacy

Maternal breastfeeding self-efficacy will be assessed using the Breastfeeding Self-Efficacy Scale–Short Form [85] in the main questionnaire. This is a validated 14-item questionnaire with a 5-point Likert scale (1=not confident to 5=very confident) to determine the participant’s confidence in their ability to breastfeed. Total scores range from 14 to 70, with higher scores indicating higher level of breastfeeding self-confidence.

##### Health History

Maternal and infant health history will be collected in the main questionnaire. Questions about birth and breastfeeding experience, breastfeeding support and practices, infant gestational age, parity, current medications or medical conditions, use of supplements, maternal dietary pattern and appetite, breast surgery, and return of menses will be included to determine their potential impact on human milk intake.

The main questionnaire will also include questions about breastfeeding practices, such as the average number of breastfeeds in 24 hours, whether participants are breastfeeding on demand or on a schedule, how much the infant spills, and questions on previous breastfeeding experience. Maternal stress will be assessed using the Global Measure of Perceived Stress Questionnaire [86].

Questions about nipple or breast trauma will be asked at visit 1 and repeated at subsequent visits (visits 2 to 4) to determine whether any changes occurred during the study period. Breastfeeding pain and maternal experience with D-MER will be assessed at visit 5 (final) with the IBCLC.

Breastfeeding pain will be the mother’s self-reported usual pain during a breastfeed on a scale of 0 (no pain) to 10 (worst pain). If pain is reported as greater than 0, follow-up questions will be asked about the type of pain, timing, frequency, and its impact on breastfeeding. This will be assessed separately from the questions around nipple or breast trauma, as those focus on damage and injury rather than general pain. Presence of D-MER will be assessed using the validated D-MER questionnaire [59]. Those who are experiencing symptoms of pain or D-MER will be offered further support by the IBCLC based on clinical judgement.

##### Nicotine and Cannabis Use

Questions about nicotine use will be assessed in the main questionnaire. Due to the rising rates of electronic cigarette (“vape”) use in New Zealand [87] and internationally [88], as well as evidence that use could be negatively associated with breastfeeding duration [89], questions on cigarette and electronic cigarette use will both be included. The number of cigarettes per day, as well as the use, nicotine level, and flavor of electronic cigarettes, will be assessed via questionnaire.

Cannabis use will be assessed in the main questionnaire. As cannabis is illegal in New Zealand, care will be taken when asking these questions to ensure that confidentiality is maintained and participants feel safe responding. Participants will be reminded that all responses are confidential and no identifying information will be kept alongside their responses. The questions about cannabis will be optional, allowing participants to leave this section blank if they feel more comfortable. Cannabis use will be assessed via questions used previously [90], modified to include questions about use after birth, along with use during pregnancy.

##### Household Temperature and Humidity

To explore the impact of potential heat stress on infant milk intake, household temperature and humidity will be measured using a digital hygrometer (Niome) with a temperature accuracy of ±1 °C and humidity accuracy of ±5%. For participants who choose to have their visits in the home that the infant is most commonly in, the digital hygrometer will be placed in the main room of the home where the visit takes place. The household temperature and humidity will be recorded after 15 to 20 minutes, which gives the hygrometer enough time to obtain an accurate reading of the room.

### Laboratory Analyses

#### Human Milk Volume

The deuterium enrichment in saliva samples will be determined by Fourier transform infrared spectrometry (Thermo Fisher Nicolet Summit, Thermo Fisher Scientific) with a liquid accessory attachment (SPECAC Pearl and CaF_2_ 100-µm pathlength top and bottom window plates). Enrichment will be determined using a modified method described by the IAEA [24]. Previously frozen saliva samples will be thawed at room temperature for 30 minutes, inverted 4 times, and centrifuged at 1000 × g for 10 minutes.

A trained researcher will pipette 45 µL of sample (baseline or postdose) onto the cell window, close the top cell window, and measure the absorption spectrum based on settings described in the IAEA protocol [24]. Each sample will be measured in duplicate unless the difference between the 2 sample measurements is greater than 3 mg/kg, in which case a third or fourth measure will be taken until 2 measurements are less than 3 mg/kg apart. The mean of the 2 closest measurements (within 3 mg/kg) will be the calculated D_2_O at each time point.

Following the determination of D_2_O enrichment, the calculation of human milk volume, infant nonmilk water intake, and classification of exclusive breastfeeding will be determined using a validated method [32,33]. The mother’s measured height and weight and the infant’s measured length and weight (collection described above) will be used in the calculation of human milk volume.

#### Human Milk Composition

##### Macronutrients

Human milk samples will be collected from the participant on the same day of expression. Samples will be carefully mixed and aliquoted into a 10-mL collection tube and frozen within 48 hours of collection, at –20 °C. Frozen samples will be defrosted at room temperature and analyzed within 2 hours. Once samples are defrosted, they will be placed into a heating bath where they will sit for approximately 20 minutes to warm to 40 °C. When the samples have reached 40 °C, they will be mixed by inversion and homogenized using an ultrasonic processor (Miris Ultrasonic Processor).

Macronutrient composition will be analyzed using a human milk analyzer (HMA, Miris). A total of 3 mL of sample will be slowly syringed into the HMA and repeated in triplicate (3 analyzes per sample) to ensure accuracy of the reading.

The HMA uses a combination of midinfrared transmission spectroscopy principles to measure concentrations of fat, carbohydrate (lactose and oligosaccharides), and both crude and true protein in human milk, as well as providing calculated values for total solids and energy. The HMA software uses internal calibration based on chemical standard methods validated for analysis of human milk. The Röse-Gottlieb method is used for total fat [91], and Kjeldahl [92] for crude protein. True protein is crude protein multiplied by 0.8 to correct for nonprotein nitrogen. The total carbohydrate content is calculated as total solids minus fat, protein, and ash [93]. Total solids are measured by drying oven [94].

##### Minerals and Trace Elements

Minerals and trace elements will be determined following methodology used previously [22]. Specifically, minerals (sodium, magnesium, phosphorus, potassium, and calcium) and trace elements (iron, copper, zinc, selenium, and iodine) will be analyzed in the Centre for Trace Element Analysis, Department of Chemistry, University of Otago, New Zealand, by inductively coupled plasma mass spectrophotometry (Agilent 7900; Agilent Technologies). Briefly, 10 mL of quartz sub-boiling 14 N nitric acid and 1 mL of 30% hydrogen peroxide will be added to approximately 1 g of the human milk sample. Samples will be microwave-digested at 200 °C for 15 minutes and dried down to approximately 1 mL. The final sample will be diluted to 25 mL with 2% aqueous nitric acid. Precision and accuracy will be checked using in-house pooled samples and multielement reference standards (SRM 1549a, whole milk powder) from the National Institute of Standards and Technology.

### Data Management

Upon enrollment, participants will be assigned a unique identifying code (participant ID). To preserve confidentiality, during data collection all data will be recorded against the participant ID. The key linking the participant ID with the participant’s name and address will be kept secure. Although it will need to be accessible to research staff so they can attend home visits (name and address) and collect data (participant ID), research staff will only have access to health information when it is essential for specific study-related tasks.

Responses to online questionnaires will be linked to participant ID numbers. Participant IDs will also be written on biological sample tubes and recording sheets. All study data will be stored in the secure REDCap database [58]. In the unlikely event that data cannot be entered directly into the REDCap database, they will be entered on a hard-copy datasheet and later transferred into REDCap. All paper copies will be stored in a locked office.

Data will be collected following rigorous protocols and cleaned according to standard data entry procedures. Quality control visits (observations of research staff conducting visits) will be conducted by senior research staff to ensure that staff follow data collection protocols consistently. Data quality checks will be run on all entered data to check for accuracy, consistency, and completeness. The results database will be stored on research team members’ computers, all of which are password protected.

### Statistical Analysis

#### Sample Size

We anticipate a dropout rate, including incomplete data, of 20% based on recruitment and completion data from a similar recent study [95]. Therefore, we aim to recruit 150 mother–infant dyads, which is expected to result in approximately 120 with complete data. With 120 participants, mean human milk intake can be estimated to a 95% CI of SD 0.18. If the distribution of intakes is similar to previous data, this corresponds to around ±27 mL/day (ie, 3% of an estimated intake of 787 mL/day at 3 months [22]). A final sample of 120 will provide a robust sample size to estimate the correlation between human milk intake and PIMS, as well as to estimate differences between groups [96].

#### Data Analysis Plan

Human milk intakes of infants aged 3 months will be described. Perception of milk supply will be collected as a continuous scale and dichotomized to create a variable for comparing low (insufficient) perceived milk supply and high (oversupply) perceived milk supply. Regression models will be used to assess how maternal perception of human milk supply (categorical independent variable) is associated with actual human milk volumes produced by lactating participants at 3 months post partum (dependent variable). Mean differences and 95% CIs will be estimated. Similarly, the relationships between predetermined potential predictors (Table 1) of human milk intakes and actual milk intakes will be described using regression modeling. Residuals of regression models will be plotted to assess homoscedasticity and normality. Results will be presented for descriptive purposes; therefore, no adjustment for confounders will be made. However, moderation by demographic characteristics will be investigated descriptively by presenting stratified results. Data will be illustrated graphically where appropriate.

To understand whether certain factors predict breastfeeding problems, the breastfeeding assessment tool will be used. These data will be analyzed using prediction modeling techniques, including a combination of linear regression models (reporting *R*^2^), and least absolute shrinkage and selection operator regression, to understand which factors might combine to predict breastfeeding problems. In addition, if there are any modifiable factors indicated to cause breastfeeding problems, a causal inference approach to analysis will be used to determine which confounders to include in the model, including the development of a directed acyclic graph.

BMI and weight velocity between birth and age up to 5 months will be calculated from the Well Child Tamariki Ora data collected. An initial investigation will be conducted into whether infant milk intakes and infant growth over time (birth to age up to 5 months) can be used to assess human milk inadequacy (actual low milk volume) using regression models.

Statistical analyses will be conducted under the guidance of a biostatistician using Stata (version 18; StataCorp LLC) software.

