#### Breastfeeding Observation

A one-off breastfeeding will be observed in the final visit (visit 5) by an IBCLC. The IBCLC will use the Bristol Breastfeeding Assessment Tool [63] to assess adequate latch and transfer of milk by the infant. This tool has 4 main elements, scoring a breastfeeding on positioning, sucking, swallowing, and attachment. A score of 0 (poor feeding elements) to 8 (good feeding elements) will be recorded by the IBCLC on the standardized Bristol Breastfeeding Assessment Tool form [63].

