#### Potential Predictors of Human Milk Intake

##### Overview

Human milk intake is complex and can be influenced by a range of different factors. A selection of potential maternal and infant factors that may influence human milk intakes has been identified through literature searches and advice from breastfeeding experts. These are summarized in Table 2.

**Table 2 table2:** Potential predictors (maternal and infant) of human milk intakes.

Factors that potentially predict human milk intakes		Explanation of potential impact or hypothesis	References

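### R-squared reported alongside LASSO in about 120 dyads can be clearly optimistic, and the prediction exercise is the only described source for nominating causes of breastfeeding problems (minor)

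*Protocol article*

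**What the plan says.** All references are to the protocol article.

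- **Outcome.** Under Breastfeeding Observation, a lactation consultant scores one observed feed at visit 5 with the Bristol tool: "A score of 0 (poor feeding elements) to 8 (good feeding elements) will be recorded". The Data Analysis Plan uses this tool to study breastfeeding problems.
- **Prediction step.** The Data Analysis Plan combines linear regression, for which R-squared is to be reported, with "least absolute shrinkage and selection operator regression, to understand which factors might combine to predict breastfeeding problems". R-squared is the only performance measure named.
- **Causal step.** The next sentence reads "if there are any modifiable factors indicated to cause breastfeeding problems, a causal inference approach to analysis will be used". A directed acyclic graph (DAG) is to be developed to choose the confounders. The text does not say what would supply the indication of cause.
- **Size.** Under Sample Size, "we aim to recruit 150 mother–infant dyads, which is expected to result in approximately 120 with complete data". The only precision figure is for mean milk intake. None is given for a prediction model.
- **Candidate predictors.** Table 2 is titled "Potential predictors (maternal and infant) of human milk intakes". No list is given for the breastfeeding-problem model.

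**The concern.** Two features of the stated analysis deserve attention.

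The first is the performance figure. R-squared from a regression fitted to the dyads that also chose its predictors rises with the number of candidates, even when none matters. With about 120 dyads and a candidate list that may be long, the rise is not negligible.

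The second is the rule that opens the causal step. It is conditional, it follows directly on a prediction exercise, and only one cohort is described. The DAG chooses confounders, but it is not used to decide which factors are examined. Read as written, a factor's predictive showing can serve as its indication of cause. LASSO is not built for that purpose: among correlated variables it may keep a proxy and drop the cause.

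At stake is a report that measured factors explain a fair share of breastfeeding problems, and that names modifiable causes, when a new sample would support neither. The Discussion intends the study's results to help shape clinical practice, so a wrongly named cause would matter.

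**Working it through.** **1. The plan's own figures.** Inputs, from Sample Size: 120 complete dyads, 20% loss, ±27 mL/day, mean 787 mL/day.

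- Half-width of the 95% CI in SD units: 1.96/√120 = 0.179 (0.181 with the t quantile). Stated: 0.18.
- Implied SD: 27/0.18 = 150 mL/day.
- Relative precision: 27/787 = 3.4%. Stated: 3%.
- Recruitment: 120/(1 − 0.20) = 150. Stated: 150.

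All reproduce. None bears on the prediction model.

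**2. Uncorrected R-squared with no signal.** For a linear model with intercept and p predictors unrelated to the outcome, E[R²] = p/(n − 1). This needs only that the outcomes be exchangeable, not normal, so the bounded 0 to 8 score does not alter it. With n = 120:

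- p = 10: 10/119 = 0.08
- p = 20: 20/119 = 0.17
- p = 30: 30/119 = 0.25
- p = 40: 40/119 = 0.34

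The value of p is an assumption. Table 2 has 30 rows (21 maternal, 9 infant), but they concern milk intake.

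**3. Selection followed by refitting.** Simulation: 300 replicates per scenario, n = 120, 30 independent normal predictors, LASSO penalty at the minimum 10-fold cross-validation error, then ordinary least squares on the selected predictors in the same data. Performance was checked on 3,000 new observations per replicate. The two scenarios with signal have five true factors of equal effect.

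| True R² | Mean number selected (of which noise) | Apparent R² after refit | R² on new data | Selected noise factors with p < 0.05 | Mean coefficient of selected true factors ÷ truth |
|---|---|---|---|---|---|
| 0 | 1.8 (1.8) | 0.06 | −0.06 | 47% | – |
| 0.10 | 6.7 (4.4) | 0.20 | −0.08 | 29% | 1.45 |
| 0.25 | 11.3 (6.8) | 0.37 | 0.07 | 21% | 1.01 |

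Full least squares on all 30 predictors with no signal gave 0.25 apparent, as the formula predicts, and −0.35 on new data.

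**4. Would adjusted R-squared be enough?** Putting the averages for true R² 0.25 into the usual formula gives roughly 1 − (1 − 0.371) × 119/(120 − 11.3 − 1) = 0.31, against 0.07 on new data. The adjustment counts the predictors kept, not the search that found them.

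**5. The causal rule.** Set side by side, the prediction sentence asks which factors combine to predict, and the next sentence acts on factors thought to cause. Nothing in that paragraph connects the two except their order. In step 3, between 21% and 47% of the selected noise factors would look significant in a naive refit, against a nominal 5%. Such factors could therefore pass into the causal step.

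**The case against.** The strongest reply is that several sharper readings are inferences the article does not support. Most of it stands.

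- **R-squared is in-sample.** A reader might infer this, but the article does not say whether the figure is apparent, adjusted or cross-validated. LASSO tuning and validation are details an article commonly leaves to a fuller plan, so their absence is not the point here.
- **LASSO selection triggers the causal analysis.** The article does not say so. It leaves the source of the indication open and gives confounder choice to a DAG, which partly separates prediction from causation.
- **Selected effects will be overstated.** This is too strong. At true R² 0.25 the refitted coefficients of true factors averaged 1.01 times the truth. The article also describes no refit after selection and no confidence intervals for this model.
- **Table 2 is the candidate list.** It is headed as predictors of intake, a different outcome, hence the range of 10 to 40.
- **A linear model is wrong for a 0 to 8 score.** That is a preference. Linear models for sum scores are common, and the Data Analysis Plan has residuals plotted for its regression models.
- **The aim is exploratory.** Predicting breastfeeding problems is neither the primary objective nor one of the five secondary objectives, and no sample size depends on it.

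The reply leaves two things standing. R-squared is the one performance figure named for an exercise that includes selection in a single modest cohort. The conditional causal rule is written into the plan, and the only work on breastfeeding problems described before it is predictive.

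**Conclusion.** The point holds as a minor one. An uncorrected R-squared at this size can be clearly optimistic: 0.08 to 0.34 in expectation with no signal and 10 to 40 candidates, and 0.37 apparent against 0.07 on new data in the simulated case with 30 candidates and true R² 0.25. The causal rule is loosely fixed, because it allows a predictive result to stand as the indication of cause and to be followed up in the same dyads.

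These sizes rest on about 120 complete dyads, an assumed number of candidates and, for the simulation, independent normal predictors, a cross-validated penalty and an uncorrected refit. A different candidate list or correlated predictors would change them. The documents do not show that the reported figure will be uncorrected or that LASSO output will be the trigger, so the conclusion is that overstatement can occur, not that it will. No stated figure is wrong, and the primary objective is untouched.

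**What to change.** Four changes to the Data Analysis Plan:

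1. State that the reported R-squared is bootstrap optimism-corrected or cross-validated, with the whole selection step, including the choice of penalty, repeated in each resample or fold.
2. List the modifiable factors of interest and draw the DAG before anyone sees the prediction results.
3. Estimate the effect of each listed factor with its DAG adjustment set, whether or not the prediction model selects it.
4. Label the prediction and causal results for breastfeeding problems as exploratory.

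The cost is a few sentences of plan text, a little more analysis work and a reported R-squared that will usually be lower. No new data are needed. There is time: the Results section gives 91 enrolled on January 17, 2026, with analysis to be completed by February 2027.

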## Results

This study was funded in April 2023 by the Health Research Council of New Zealand (grant 23/461). Recruitment for this study began in February 2025 and is currently underway. As of January 17, 2026, a total of 91 participants have been enrolled. Recruitment is anticipated to conclude in June 2026, with analysis expected to be completed by February 2027. Final results are anticipated to be disseminated in late 2027 following completion of data analysis.

## Discussion

This study will explore the relationship between maternal perception and actual milk quantity and quality, providing significant implications for improving breastfeeding support. If PIMS is linked to specific physiological characteristics of human milk, such as lower volume or suboptimal nutrient concentrations, this could provide a biological basis for potentially individualized interventions to support the continuation of breastfeeding. Alternatively, if perception is not linked to measurable differences, this would reinforce the need for better psychosocial support and education to sustain breastfeeding, or the development of tools that can be used to assess milk supply and reassure mothers that their supply is sufficient. Because perception is a modifiable factor, identifying its relationship to human milk volume and composition offers a critical opportunity to intervene early, support breastfeeding continuation, and improve infant and maternal health outcomes.

To the best of our knowledge, there is currently no published research using the DTM technique to investigate whether PIMS is related to actual milk insufficiency, nor has the association with nutrient composition been investigated, a gap in the literature as highlighted by the 2023 Lancet Series on Breastfeeding [51]. While 1 study has investigated the relationship between perceived and actual milk insufficiency [20], it was restricted to first-time mothers and used test-weighing methods to estimate infant milk intake, both of which inherently limit the interpretation of the findings.

The main strength of MABBS is the use of the DTM stable isotope technique for estimating human milk volume in relation to mothers’ perception of milk supply. This methodology is considered to be the gold standard, allowing the most accurate reporting of infant milk intake [33]. This is particularly important given our large sample size (at least 120 participants), which allows us to determine daily infant milk intake to an accuracy of ±27 mL/day. Finally, we aim to recruit a diverse population with good ethnic representation to ensure that the outcomes are relevant to all people living in New Zealand.

This study also has some limitations. A narrow age range of participants (those with babies aged 2 to <4 months) was required because of the variation in milk intake at different stages of lactation. While this is necessary for the methodology of this study, it may impact our ability to capture participants with a wide range of perception of milk supply. Furthermore, while the research team aim to make the results relevant to the New Zealand population, due to differences in populations, the findings of this study may not be generalizable to people in other countries outside New Zealand.

We will disseminate the results of this study through multiple channels. For academic dissemination, the results will be published in open-access and high impact journals, as well as presented at relevant conferences. However, it is of high importance to members of the research team to ensure that results are also useful to inform practice at a clinical level. With help from the advisory group and experts in this space, results will be shared with those working with breastfeeding families to help shape clinical practice. This may include webinars or resources specifically designed for health professionals to inform personalized intervention strategies for breastfeeding parents.

